### Statistical analyses

Unless otherwise specified, analyses use an ITT approach that analyzes individuals by treatment assignment. We will use descriptive statistics to summarize demographic data, tobacco use history, and other baseline characteristics. Summaries will be generated for the entire sample and by treatment arm. Given the randomized design, we will not assess for significant baseline treatment differences. With the exception of the stratification variable, no covariate adjustment will be included in the primary analysis. For all exploratory analyses, two-tailed *p* values will be reported with no adjustment for multiple comparisons. In all cases, findings will be reported using point estimates and corresponding 95% CIs. Model assumptions for each analysis will be validated and transformations or non-parametric methods will be utilized as appropriate.

#### Aim 1 (Effectiveness) analyses

The primary outcome of biochemically confirmed point-prevalence abstinence at 12 months post randomization will be analyzed using ITT. The primary analysis of the smoking outcomes will be performed using logistic regression. Separate analyses will be performed for each abstinence endpoint. For the logistic regression analyses, the dependent variable will be smoking abstinence and the independent variable will be treatment (WEB + TXT + TTS vs WEB + TXT vs UC). Study site will be included as a covariate in the primary analyses. We hypothesize that WEB + TXT + TTS will yield higher quit rates than WEB + TXT and UC and that WEB + TXT will yield higher quit rates than UC. To test these hypotheses, all pairwise comparisons of the three treatment groups will be performed. For the primary analysis of smoking abstinence outcomes, any individual who misses a visit will be classified as smoking for that assessment. This approach is used because the data are assumed to be missing not at random (MNAR). However, this approach is sensitive to differential attrition across treatment groups and tends to overestimate the precision of the estimate of the treatment effect. Therefore, to supplement primary analysis we will perform sensitivity analysis using multiple-imputation based on pattern-mixture models under the MNAR assumption (SAS/STAT version 13.2, PROC MI and PROC MIANALYZE). Multiple imputations of missing abstinence outcomes will be imputed using the logistic regression method, with the outcome adjusted by modifying the log odds ratios (OR) [105, 106]. Since the OR relating missingness to smoking is not known, we will conduct a sensitivity analysis to assess its impact on the estimate and significance of the treatment effects.

We will examine potential moderators (e.g. screening result, gender, age) by analyzing interactions between treatment and selected variables. We will examine treatment/moderator interaction term on outcomes after entering main effects. We will also explore moderators of the relationship between treatment assignment and treatment utilization.

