#### WEB + TXT + TTS intervention

Initiation of the WEB + TXT intervention in this arm is identical to the approach described above. Unique to this treatment arm is a required session with a TTS before LCS. During this session, the TTS will conduct an assessment, formulate a treatment plan, and provide counseling, education, and arrange for follow-up. TTS counselors will be able to view real-time utilization data from BecomeAnEX through the BOSS Registry, already part of their routine workflow. They will know which elements of the website the participants have used/not used and will be able to incorporate this information into the counseling session. The TTS will utilize motivational interviewing skills and strategies to create momentum for quitting and actively engage the patient. TTS counseling incorporates information gathered from an assessment to collaboratively develop an individually tailored treatment plan that consists of cognitive and behavioral strategies and pharmacological treatment. An interactive patient treatment guide will be used to standardize the educational and counseling content. At the conclusion of this initial session, the TTS will schedule four additional sessions.

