### Power calculation

Positive (i.e. abnormal) LCS findings increase the odds of abstinence [6, 97–99]. Therefore, to be conservative in our sample size calculations, efficacy estimates for UC are based on data from patients in previous trials with negative screening results. Among patients with negative findings in the National Lung Screening Trial, one-year abstinence rates are in the range of 9.7% [100] to 12.6% [97]. In the Danish Lung Cancer Screening Trial [98], patients received < 5 min of counseling from a nurse and 30-day abstinence at one-year follow-up was 11.4% among patients with no significant LCS findings. Cox et al. [101] reported seven-day abstinence at one year of 13%. Brief counseling for smoking cessation (<3 min) yields six-month abstinence rates of 13.4% [43]. Therefore, we conservatively estimate that biochemically verified abstinence at 12 months for UC will be 10%.

Efficacy estimates for WEB + TXT are based on several converging lines of evidence: (1) two meta-analyses have reported statistically significant effects of interactive and individually tailored interventions compared to usual care or written self-help (relative risk [RR] = 1.48, 95% confidence interval [CI] = 1.11–2.78 [30]; RR = 2.10, 95% CI = 1.25–3.52 [33]; (2) a meta-analysis by Webb et al. [102] found that the use of TXT in Internet interventions had large effects on behavior change (d = 0.81, k = 4); (3) combined Internet and TXT interventions yielded six-month sustained abstinence of 17.1% in Borland et al. [103] and 12-month repeated point prevalence abstinence of 20% in Brendryen et al. [46]. Therefore, we conservatively estimate that biochemically verified abstinence at 12 months for WEB + TXT will be 16%.

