Efficacy estimates for WEB + TXT + TTS are also based on several lines of evidence: (1) abstinence reported by Fiore et al. [43] for treatment duration of 31–90 min (comparable to the TTS visit that will occur before LCS) was 26.5% (95% CI = 21.5–31.4); (2) among more than 6000 patients who received TTS counseling in the NDC outpatient clinic, seven-day point prevalence abstinence at six months under intention-to-treat (ITT) analysis was 28.1% (95% CI = 27.7–30.1) [60]; (3) in a pilot study of LCS patients who completed a TTS visit before LCS, seven-day abstinence at six months (ITT) was 34% [64]; (4) previous studies of combined Internet and TTS counseling interventions have yielded quit rates (30-day point prevalence abstinence under ITT) of 21.5% [29] to 53% [69] with a strong dose-response relationship for the number of TTS sessions. Therefore, we conservatively estimate that biochemically verified abstinence at 12 months for WEB + TXT + TTS will be 24%.

For pairwise treatment comparisons, we will use the Holm–Šídák approach to account for multiple comparisons [104]. The three pairwise comparisons will be performed with two-tailed *p* values obtained which are not adjusted for multiple comparisons. These *p* values will be ranked from smallest to largest. If the smallest *p* value is > 0.0167 we will conclude that none of the comparisons is statistically significant. If the smallest *p* value is ≤ 0.0167 this comparison will be considered statistically significant and the second smallest *p* value will be evaluated. If the second smallest *p* value is > 0.025, we will conclude that the final two comparisons are not statistically significant. If the second smallest *p* value is ≤ 0.025, this comparison will be considered statistically significant and the final *p* value will be evaluated using *p* ≤ 0.05 to denote statistical significance. For our hypothesized abstinence rates, a total sample-size of 1650 (550/group) will provide statistical power ≥ 99% for the overall comparison across treatment groups and > 85% for each of the three pairwise treatment comparisons.

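### The stated primary model and power make no allowance for participants in the WEB + TXT + TTS arm sharing a counsellor; if counsellors matter, both TTS contrasts look more precise than they are

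*Protocol article*

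**What the plan says.** All references are to the Protocol article.

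- **Treatment.** Under WEB + TXT + TTS intervention: "Unique to this treatment arm is a required session with a TTS before LCS". After that session, "the TTS will schedule four additional sessions". The section speaks of counsellors in the plural but gives no number or caseload, and does not say that one counsellor delivers all five sessions. A treatment guide standardises the content.
- **Primary model.** Under Aim 1 (Effectiveness) analyses, the model is a logistic regression where "the dependent variable will be smoking abstinence and the independent variable will be treatment (WEB + TXT + TTS vs WEB + TXT vs UC"), with study site as covariate. Under Statistical analyses: "With the exception of the stratification variable, no covariate adjustment will be included in the primary analysis". No counsellor term, random effect, clustered variance or ICC appears.
- **Power.** Under Power calculation, 1650 participants are said to give at least 99% for the three-arm test. The pairwise claim is "> 85% for each of the three pairwise treatment comparisons". The inputs are 10%, 16% and 24% abstinence and 550 per arm. No design effect is mentioned.
- **Reach of the claim.** Study setting lists seven sites (four, two and one) and presents their variety as securing generalisability to other healthcare systems and screening programmes.

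**The concern.** Participants are randomised individually, but one arm is then treated by a limited set of counsellors, each seeing many of its 550 participants. This is a partially nested design. If some counsellors obtain higher quit rates than others, outcomes within a caseload are correlated, and the quit rate in that arm is less precisely known than 550 independent observations would imply. The site covariate does not absorb this: a site term shifts all arms at a site equally, whereas a counsellor effect acts within the arm assigned counselling.

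The contrast most exposed is WEB + TXT + TTS vs WEB + TXT, part of Hypothesis 1a. It shows whether the costlier component adds anything, and it feeds the incremental cost per quit. A few unusually effective counsellors could be read as an effect of specialist counselling in general.

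**Working it through.** **1. The plan's own figure.** Independent participants, n = 550 per arm, two-sided 0.05, power = Φ(d/SE − 1.96), with SE² = p₁q₁/550 + p₂q₂/550.

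- 16% vs 10%: SE 0.0202, power 84.4% (84.2% pooled, 84.5% arcsine).
- 24% vs 16%: SE 0.0240, power 91.5% (91.4% pooled).
- 24% vs 10%: power > 99.9%.

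Simulating the stated step-down rule gives 84.3%, 91.1% and > 99.9%. The stated pairwise figure is therefore matched to within about one point with no design effect, which is consistent with independence having been assumed.

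**2. Assumptions needed.** The article gives no ICC and no counsellor count. I assume 1, 2 or 4 counsellors at each of the 7 sites (7, 14 or 28 in total, so m = 550/7 = 78.6, 550/14 = 39.3 or 550/28 = 19.6 participants each) and an ICC from 0.005 to 0.05.

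**3. Formulas.** Design effect in the TTS arm only: DE = 1 + (m − 1) × ICC.

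- Type I error of the planned test at nominal 0.05, equal rates: the true variance is (1 + DE)/2 times the model variance, so the error is 2 × [1 − Φ(1.96/√((1 + DE)/2))].
- Power of a test that respects the clustering: SE² = DE × p₁q₁/550 + p₂q₂/550, where p₁ is the TTS arm, with a normal reference.

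**4. One case in full: 14 counsellors, ICC 0.02.** DE = 1 + 38.3 × 0.02 = 1.77. Variance ratio (1 + 1.77)/2 = 1.38; type I error 2 × [1 − Φ(1.96/1.176)] = 9.6%. For 24% vs 16%: SE² = 1.77 × 0.24 × 0.76/550 + 0.16 × 0.84/550 = 0.00083, SE = 0.0288, power Φ(0.08/0.0288 − 1.96) = 79%.

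**5. Full range (7 / 14 / 28 counsellors).**

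| ICC | DE | Type I error at 0.05 | Power, 24% vs 16%, at 0.05 |
|---|---|---|---|
| 0 | 1 | 5% | 91.5% |
| 0.005 | 1.39 / 1.19 / 1.09 | 7.3 / 6.1 / 5.5% | 85 / 89 / 90% |
| 0.01 | 1.78 / 1.38 / 1.19 | 9.6 / 7.3 / 6.1% | 79 / 85 / 89% |
| 0.02 | 2.55 / 1.77 / 1.37 | 14.1 / 9.6 / 7.2% | 68 / 79 / 86% |
| 0.05 | 4.88 / 2.91 / 1.93 | 25.3 / 16.1 / 10.6% | 46 / 63 / 77% |

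The normal reference is generous when counsellors are few. A t reference with counsellor-based degrees of freedom gives 59 / 76 / 85% at ICC 0.02 and 37 / 59 / 75% at ICC 0.05. If the contrast is judged at the 0.025 step, power under independence is 86% and falls to 78% at ICC 0.01 with 14 counsellors.

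**6. Does site adjustment help?** A simulation of the site-stratified (Mantel–Haenszel) test with 7 equal sites held about 5% at ICC 0. With 14 counsellors it gave 6.2%, 7.3%, 9.6% and 16.6% at ICC 0.005, 0.01, 0.02 and 0.05, close to the formula. It does not help.

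**7. Contrast with usual care.** For 24% vs 10% at 0.0167, power is 96% or more everywhere except 7 counsellors with ICC 0.05, where it is 82%.

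**The case against.** A reader might infer that outcomes in this arm are known to be clustered, that the true type I error is as high as 25%, and that the pairwise power is simply false. The documents do not support that.

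- **No ICC, counsellor count or caseload is given.** Shared caseloads and participants who never attend would weaken any clustering. Content is standardised by a guide, and the audio fidelity review is a control on variation, so it is not evidence of it.
- **The inflation depends on the target of inference.** If counselling affects nobody, the planned test is valid. If the counsellors are regarded as fixed and their average effect is zero, simulation gives 4.7–5.0%. The excess arises only when they stand for a wider population. That is a choice of estimand, though one that the generalisability claim under Study setting implies.
- **The upper end is demanding.** At a mean of 16%, ICC 0.05 means true counsellor quit rates spread from about 4% to 35% (95% range); ICC 0.01 still means about 10% to 24%. With one counsellor per site, the effect is indistinguishable from treatment-by-site heterogeneity.
- **The other arms are not wholly free of it.** Usual care participants are referred passively to the same institution's specialist services, and some may see the same counsellors.
- **The analysis plan is not shown.** A random effect or clustered variance is not covariate adjustment, so the article does not rule one out.

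These points limit the size. They do not reverse the direction: with a positive ICC and a generalising aim, the stated model errs towards too much precision. Nor would a later analysis plan alter the article's power statement, which carries no condition on counsellor effects.

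**Conclusion.** The concern holds in conditional form. The stated model and power ignore a possible counsellor correlation in the one arm assigned counselling, and the site covariate does not replace that allowance. The conclusion requires a positive ICC and inference beyond the particular counsellors.

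At ICC 0.005–0.01 with 14–28 counsellors the effect is modest: type I error about 5.5–7.3%, and power for TTS added to WEB + TXT still about 85–90% at 0.05. At ICC 0.02 with 14 or fewer counsellors, or at ICC 0.05 throughout the assumed range, it is material and could change the conclusion on that part of Hypothesis 1a. The contrast with usual care remains well powered, and WEB + TXT vs usual care is not directly affected.

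**What to change.** 1. Record which counsellor delivers each participant's first TTS session. Confirm that the BOSS Registry holds this, because the listed extracts cover session number and duration but not counsellor identity. Treat participants who never attend, and those in the other two arms, as singletons, so that everyone stays in the arm assigned.
2. For the two TTS contrasts, prespecify a partially nested analysis: a random counsellor effect in the TTS arm only, or counsellor-clustered variance with a small-sample correction. With about 7 counsellors, robust variance is fragile and the correction is essential. It need not replace the primary model. At the least it should be a sensitivity analysis that must be reported beside the primary result and considered before Hypothesis 1a is claimed.
3. State the number of counsellors and an assumed ICC, and give the power for WEB + TXT + TTS vs WEB + TXT as conditional on them.

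Cost: analysis-plan wording and one extra variable, with no added participants or visits. The downside is wider intervals for the TTS contrasts and a less favourable stated power for one of them.

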#### Aim 2 (Implementation) analyses

First, we will examine treatment uptake and engagement via self-reported treatment use (behavioral or pharmacologic) and automated tracking data from the BecomeAnEX WEB and TXT program at each follow-up interval. We will test whether proactive enrollment in treatment yields higher levels of treatment uptake and engagement than AAR UC using descriptive statistics. We hypothesize that overall utilization will be higher for participants proactively enrolled in WEB + TXT compared to participants provided passive referrals to the same interventions in UC. Next, we will examine whether treatment engagement mediates the treatment-outcome relationship. To assess whether treatment engagement is predictive of improved abstinence outcomes and whether treatment engagement mediates the treatment effect, we will perform a series of additional logistic regression analyses following the framework described by Baron and Kenny [107]. The Aim 2 analytic plan is depicted in Fig. 2.

**Fig. 2 Fig2:**
[figure not shown]
Mediational model

Here, X is the exogenous variable (treatment), Z is the hypothesized mediator (treatment engagement), Y is the outcome (abstinence at month 12), a is the regression path between treatment and the mediator, b is the regression path between the mediator and the outcome, and c’ is the regression path between treatment and the outcome controlling for the effect of the mediator.

To test mediation hypotheses, we will use the approach described by MacKinnon and Dwyer for binary mediator and outcome variables [108]. We will establish mediation as follows: (1) logistic regression will assess whether the effect of treatment assignment on abstinence is statistically significant; (2) logistic regression will assess whether the effect of treatment assignment on treatment use is statistically significant; (3) multivariable logistic regression will determine whether treatment use is statistically associated with abstinence after adjustment for treatment assignment; and, (4) we will assess whether the effect of treatment assignment on outcome is significantly attenuated in magnitude relative to step 1.

We will compare total and incremental costs to implement each intervention from a payer perspective. Implementation costs of the two interventions will be estimated using average market values for salaries of the additional staff needed to perform the TTS counseling and market costs of the digital intervention. If a treatment effect is observed, we will assess cost per quit and incremental cost per quit. Cost-effectiveness of the two proposed study interventions compared to usual care will be estimated by employing a Markov Model [109, 110]. Hypothetical cohorts representing the U.S. population will be simulated through long-term screening. Disease progression will be modeled with transition probabilities of developing lung cancer. Model parameters not directly measured in the proposed trial will be supplemented with data from the literature, including the publicly available Lung Cancer Policy Model of the Cancer Intervention and Surveillance Modeling Network [111–113]. Model complexity specific to our modeling environment will be determined by available data for the model parameters. A simplistic design not incorporating smoking status (current vs smoker) will be used as the model basis. Smoking status will be incorporated if identified data prove to make this feasible. If not feasible, the simplistic model design will serve as a crucial starting point for further analyses in the future. Sensitivity analyses will be conducted to determine the impact of changes in key model inputs.

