#### WEB + TXT intervention

The site Study Coordinator will conduct brief cessation counseling (<3 min) and then proactively enroll participants in the digital intervention using a study-specific enrollment page on BecomeAnEX. After locating the participant in the BecomeAnEX database using a unique study identifier, the Study Coordinator will assist the participant in completing registration for the WEB and TXT program and provide a brief orientation about both interventions.

The BecomeAnEX website is Truth Initiative’s smoking cessation program that was launched in 2008 [75, 76]. The program was designed around national guidelines for tobacco dependence treatment [43] and principles of social cognitive theory [77]. A national mass media campaign [75] and ongoing online advertising have resulted in over 800,000 registered users since its inception. BecomeAnEX educates smokers about the behavioral and pharmacologic aspects of nicotine addiction and provides tools to enhance self-efficacy for quitting. It guides and supports smokers through a series of interactive components that assist users in selecting a quit date, identifying their smoking triggers, developing coping skills, and selecting a cessation medication. The site also includes a large social network comprising thousands of current and former smokers who interact via several asynchronous communication channels. All user actions are date- and time-stamped and stored in a relational database. BecomeAnEX was extensively pilot tested during development [75] and designed around website usability best practices, making it appropriate for use by older adults [78–81].

The BecomeAnEX TXT program is a fully automated system that has been integrated into the website. The TXT program is also based on social cognitive theory [77]. Messages are tailored around a user-entered quit date and provide general quitting advice, positive reinforcement, motivation, reminders to avoid smoking cues and triggers, and information about nicotine and withdrawal. Keywords (e.g. “CRAVE,” “MORE”) generate on-demand support and information and “STOP” terminates the program at any time. The program delivers three weeks of once-daily cessation text messages regardless of whether a user sets a quit date. When a user sets a quit date, they receive two weeks of twice daily messages pre-quit date and six weeks of 1–3 messages/day post quit date, with periodic messages at cessation milestones (e.g. six months post quit date).

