#### Process variables

Treatment utilization will be assessed via self-report at each follow-up and automated tracking metrics extracted from BecomeAnEX and the BOSS Registry. At each follow-up, participants will be asked about their use of any cessation methods. The following metrics will be extracted from BecomeAnEX: total time spent logged into the website; number of return visits; use of the static content and videos; use of interactive components/tools; number of replies to interactive text messages; unsubscribe rates; modal day of unsubscribe; number of days enrolled in TXT; and number of text messages received. The following metrics will be extracted from BOSS regarding completion of TTS counseling: number and duration of completed TTS counseling sessions; tobacco use status; confidence and importance for quitting or maintaining abstinence; medication use; cravings/urges and management strategies.

TTS intervention fidelity will be monitored throughout the study via review of digital audio recordings. Audio review will be conducted using a fidelity measure based on the Mayo Clinic treatment model including items adapted from the Motivational Interviewing Treatment Integrity Code [60].

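### The Aim 2b mediation test is fixed to a yes/no mediator although engagement is recorded mostly as counts and times, which discards graded information and lowers power for the mediator path

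*Protocol article*

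**What the plan says.** The mediational model under Aim 2 (Implementation) analyses states that mediation will be tested with a published approach for "binary mediator and outcome variables". Two of its four steps show that the mediator must be yes/no:

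- Step 2, treatment to mediator: "logistic regression will assess whether the effect of treatment assignment on treatment use is statistically significant".
- Step 3, mediator to outcome: "multivariable logistic regression will determine whether treatment use is statistically associated with abstinence after adjustment for treatment assignment".

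The legend to the model describes the mediator only in general terms: "Z is the hypothesized mediator (treatment engagement". No rule is given for turning the recorded measures into yes or no.

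Process variables lists what will be extracted, starting with "total time spent logged into the website; number of return visits; use of the static content and videos; use of interactive components/tools". It continues with text replies, days enrolled, messages received, and the number and duration of TTS sessions. Most of these are graded. Hypothesis 2b, in the Background, concerns an increase in treatment use, and Hypothesis 2a concerns its level.

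In the WEB + TXT arm the coordinator will "proactively enroll participants in the digital intervention using a study-specific enrollment page on BecomeAnEX" and helps the participant complete registration. Daily texts then run for three weeks whether or not a quit date is set. The WEB + TXT + TTS arm starts the same way and adds a required TTS session. UC participants are passively referred to the same program, and their digital use is tracked comparably.

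**The concern.** The hypothesis is about how much treatment people use, but the stated test sees only whether they use it. Two separate losses can follow.

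1. **Information.** Someone who returns once and someone who returns thirty times may receive the same code, so the dose-related part of the association with abstinence is lost.
2. **Overlap with arm.** If the cut is low (registered, received a text, any use), almost everyone in the digital arms meets it by design. Step 3 must then separate use from arm with little independent variation left.

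At stake is a missed or very imprecise answer to Hypothesis 2b, a named hypothesis under one of the three aims. The primary outcome and the Aim 1 tests do not depend on it.

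**Working it through.** **Inputs from the article.** 550 per arm; assumed 12-month abstinence 10% (UC), 16% (WEB + TXT) and 24% (WEB + TXT + TTS); missing counted as smoking, so all 550 per arm stay in.

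**The plan's own figure.** The only stated power is for Aim 1: at least 99% overall and more than 85% for each pair. Simulating the stated step-down rule with a pooled two-proportion test gives 84.3% (10 v 16%), 91.2% (16 v 24%) and over 99.9% (10 v 24%), with overall power above 99.9%. The lowest is within a point of the stated floor, so the inputs are read correctly. No power, use rate or effect size is stated for Aim 2b. Everything below rests on assumed values.

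**Step 1: collinearity of a binary mediator with arm.** With use proportions m0 (UC) and m1 (digital), equal arms and m̄ = (m0 + m1)/2:

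φ = [(m1 − m0)/2] / √[m̄(1 − m̄)], variance inflation = 1/(1 − φ²), standard-error inflation = its square root.

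Example, m0 = 0.10 and m1 = 1.00: m̄ = 0.55; φ = 0.45/√0.2475 = 0.905; variance inflation 5.5; standard-error inflation 2.3.

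| Use UC / digital | φ | Variance inflation | SE inflation |
|---|---|---|---|
| 10% / 100% | 0.90 | 5.5 | 2.3 |
| 20% / 100% | 0.82 | 3.0 | 1.7 |
| 10% / 95% | 0.85 | 3.6 | 1.9 |
| 20% / 95% | 0.76 | 2.4 | 1.5 |
| 10% / 50% | 0.44 | 1.24 | 1.1 |
| 20% / 60% | 0.41 | 1.20 | 1.1 |

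Near-duplication appears only when almost all digital-arm and few UC participants count as users. Approximate Wald power for the mediator path (assumed odds ratio 2.0, arm totals held at 10% and 16%) shows the same: 92% at 10%/50% use, 76% at 10%/80%, 63% at 10%/90%, 39% at 5%/95%.

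**Step 2: visit counts as the true driver.** Assumed: 98% use in the digital arm and 10% or 20% in UC; users' visits 1 + negative binomial (mean 6, k 0.6); logit(abstinence) = −2.30 + 0.40·log(1 + visits); abstinence about 10% v 17%; 600 runs.

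| Mediator | Power, UC use 10% / 20% | Loss against log(1 + visits), points |
|---|---|---|
| log(1 + visits) | 95% / 98% | – |
| binary, any use | 48% / 69% | 47 / 29 |
| binary, 2 or more visits | 76% / 87% | 19 / 11 |
| binary, 3 or more visits | 84% / 92% | 11 / 6 |
| binary, 6 or more visits | 85% / 92% | 10 / 6 |

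**Step 3: a different model.** Assumed: a normally distributed engagement score, digital arm higher by 1.0 SD, arm totals fixed at 10% and 16%, 600 runs (Monte Carlo error about 2 points). The cut marks 50%, 80% or 95% of the digital arm as users.

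| Log OR per SD | Continuous | Cut 50% | Cut 80% | Cut 95% |
|---|---|---|---|---|
| 0.25 | 76% | 55% | 47% | 26% |
| 0.35 | 97% | 86% | 79% | 51% |
| 0.50 | about 100% | 98% | 98% | 81% |

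The loss runs from about 2 to 51 points. In this model the 95% cut also marks 74% of UC as users: m̄ = 0.845, φ = 0.105/√(0.845 × 0.155) = 0.29. The loss there is therefore information thrown away by an extreme cut, not collinearity. With an arm gap of 1.5 SD the losses run from about 3 to 43 points.

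**The case against.** A reader might infer that the mediator nearly duplicates treatment assignment. The article does not support that. It never sets the cut at registration or any use, registration is not among the extracted metrics, and the coordinator assists registration rather than doing it for the participant. A required TTS session is also not the same as a completed one. With moderate use rates φ is only 0.41 to 0.44. If self-reported use of any cessation method counts, UC use could be well above 20%, which would weaken the overlap further.

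Three more objections have weight. Most of the 30-to-45-point loss comes from choosing any use as the cut; at three or more visits it is about 6 to 11 points, and that binary variable is less collinear with arm than log(1 + visits) (variance inflation 1.5/1.4 against 2.0/1.7). The visit model makes log-visits the only driver of abstinence, so it favours that form by construction. And a condensed article may properly leave the cut-point to a fuller document that is not shown, so its absence is no fault.

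All of this stands, and it limits the size of the point. It does not remove the core. The binary form is stated, not left open: an analysis plan could add a cut, but could not keep the measured scale without departing from the method described. Graded engagement is summarised descriptively elsewhere in Aim 2, but the formal mediation test does not use it. In every setting tried, under both models, the yes/no version had lower power.

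**Conclusion.** The point holds in a limited form. The stated method for Hypothesis 2b reduces a mostly graded mediator to yes/no and thereby gives up power for the mediator path. In the visit model the loss is roughly 5 to 20 points with a cut at two or more visits, and roughly 30 to 45 points with a cut at any use. The normal-score model gives a wider range and shows that the size depends strongly on the cut and the effect. Use rates, effect sizes and the engagement distribution are all assumptions; the article supplies none. Near-collinearity with arm is a risk attached to a low cut, not a feature of the plan. The consequence is confined to Hypothesis 2b. Because the data are already to be collected, this is an inexpensive improvement worth making, not a threat to the trial.

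**What to change.** For WEB + TXT versus UC, make the main mediator a measure of engagement after the assisted registration session, kept on its measured scale: for example log(1 + return visits) or time online. Avoid messages received and days enrolled, which are partly automatic once someone is enrolled and could follow arm closely even as continuous variables.

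Model the mediator with linear or negative-binomial regression. Estimate the indirect effect on the abstinence-probability scale with a regression-based mediation estimator and a bootstrap 95% CI. Keep a binary mediator as a sensitivity analysis, with a prespecified cut above registration. Handle TTS sessions and medication use as separate mediators, so that restricting the main measure to digital engagement does not drop them from Aim 2.

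The cost is plan wording, analysis code and slightly more analysis work; user actions are already time-stamped and the metrics already listed for extraction. The downside is a distributional choice for skewed counts. Nothing in Aim 1 changes.
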